**Trial Protocol and Statistical Analysis Plan**

Title: Disclosure of genetic information and change in dietary intake: a randomized

controlled trial

Authors: [name] and [name]

This supplement contains the following items:

1. Summary of trial
2. Original trial protocol, final protocol, summary of changes
3. Original statistical analysis plan, final statistical analysis plan, summary of changes
4. **Summary of trial**

The purpose of this randomized controlled trial is to determine the effect of disclosing diet-related genetic information on dietary intake behaviour. Participants who completed the Toronto Nutrigenomics and Health study will be invited by e-mail to participate in this study. Informed consent will be obtained. Participants who choose to take part will be randomized into an intervention group or a control group (2:1 ratio). All participants will complete a baseline196-item food frequency questionnaire (FFQ) to assess habitual food intake over the past 30 days. Shortly after the baseline assessment, participants in the intervention group will receive a report of personalized dietary recommendations. The report will provide them with information on their gene variants that influence caffeine metabolism, sugar consumption, salt sensitivity and vitamin C metabolism. Participants provided a blood sample for the Toronto Nutrigenomics and these genotypes were determined. The report will explain what the genotypes mean and will provide DNA-based advice for daily intakes of caffeine, sugar, sodium and vitamin C. Participants in the control group will receive Health Canada’s general recommendations for intakes of caffeine, sugar, sodium and vitamin C with no genetic information. Three months after receiving the dietary recommendations, participants in both groups will complete a second FFQ to examine potential short term changes in dietary intake. A third FFQ will be collected one year after baseline, to examine potential long term changes. The nutrient analysis between the three FFQs will be compared to identify changes in dietary intake of caffeine, sugar, sodium and vitamin C. The intervention group FFQs will be compared to the control group FFQs to examine how changes differed when dietary advice was personalized based on genotype.

**Significance:** Recent advances in genomics technology have made the acquisition of personalized genetic information easily obtainable. Nutrigenomics tests offering dietary advice based on genotype are commercially available through the internet (1). A potential outcome of these genetic tests is better dietary and lifestyle habits for improved health. However, much debate exists about the influence of genetic information on lifestyle modification (2). We are pursuing research in this area to create new knowledge of how providing genetic information affects individual dietary intake behaviour.

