**Final protocol:**

Same as original protocol except 157 subjects were recruited.

S**ummary of changes:**

No changes were made to the original study protocol. 157 subjects were recruited instead of the

original goal of 200. Routine updates were made to the protocol’s trial record on

http://clinicaltrials.gov (NCT01353014) to reflect study progress (e.g. enrolment status,

anticipated follow-up and completion dates, actual follow-up and completion dates).

1. **Original statistical analysis plan**

- Subject characteristics between the intervention and control group will be compared using

a Student’s t-test for continuous variables (age) and a Chi-square test for categorical

variables (sex, ethnicity, level of education).

- General linear model will be used to identify changes in the mean intakes of caffeine,

added sugars, vitamin C and sodium from baseline to 3 months and baseline to 12 months.

- Tukey’s test for multiple comparisons will be applied to determine whether changes in

intake of the intervention risk and intervention non-risk groups differ from the change in

intake of the control group.

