**Final statistical analysis plan (changes from original plan are indicated in bold):**

- Subject characteristics between the intervention and control group will be compared using

a Student’s t-test for continuous variables (age) and a Chi-square test for categorical

variables (sex, ethnicity, level of education).

- General linear model used to identify changes in the mean intakes of caffeine, added

sugars, vitamin C and sodium from baseline to 3-months and baseline to 12-months.

- Tukey’s test for multiple comparisons applied to determine whether changes in intake of

the intervention risk and intervention non-risk groups differed from the change in intake of

the control group.

- **General linear model used to compare baseline intakes of caffeine, vitamin C, added**

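### Change in intake is tested only by setting genotype subsets of the intervention arm against the whole, unsplit control arm; neither a whole-arm contrast nor a genotype-matched contrast is specified

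*Supplement*

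**What the plan says.** The Summary of trial gives the purpose as "to determine the effect of disclosing diet-related genetic information on dietary intake behaviour". It describes two arms randomised 2:1 and then the comparison: "The intervention group FFQs will be compared to the control group FFQs to examine how changes differed". That sentence goes on to tie the comparison to advice tailored by genotype. On genotyping, the Summary says "Participants provided a blood sample for the Toronto Nutrigenomics and these genotypes were determined". The Final protocol reads "Same as original protocol except 157 subjects were recruited", against a target of 200.

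The Final statistical analysis plan has three relevant items:

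- **Whole arm against whole arm.** "Subject characteristics between the intervention and control group will be compared using" a t-test or chi-square test. This covers age, sex, ethnicity and education, not intake.
- **Intake model.** "General linear model used to identify changes in the mean intakes of caffeine, added" sugars, vitamin C and sodium, from baseline to 3 and to 12 months. No model terms or contrasts are listed.
- **Between-group test on intake.** Tukey's test is applied to the question whether changes in "the intervention risk and intervention non-risk groups differed from the change in intake of" the control group.

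The only addition in the final version is conditional adjustment for ethnicity.

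**The concern.** Randomisation makes the two arms comparable as wholes. It also makes risk carriers in one arm comparable with risk carriers in the other. It does not make risk carriers in one arm comparable with a mixture of carriers and non-carriers in the other, and that is the comparison planned.

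The planned contrast isolates disclosure only if genotype has no effect of its own on change in intake. The Summary chose these variants because they bear on caffeine metabolism, sugar consumption, salt sensitivity and vitamin C metabolism. A genotype-related difference in how intake changes is therefore possible, though the documents do not establish one. Controls also receive dietary advice, and their response to it could vary by genotype.

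At stake is attribution. A difference between the intervention-risk group and control could be read as an effect of being told one's genotype when it partly reflects having that genotype. Adjusting for ethnicity does not remove this.

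**Working it through.** The documents give no alpha, power, effect size, SD or genotype frequency, so there is no figure of theirs to reproduce.

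**Inputs**
- From the documents: 157 recruited, 2:1 allocation, three groups in the Tukey test.
- Assumed: 105 intervention and 52 control, no dropout, SD of change = 1, two-sided 0.05, 80% power, risk share *p* of 30–70% (50% in the worked lines), genotype shift *g* of 0, 0.3 or 0.5 SD, equal in both arms.
- Critical values: 1.975 for the two-arm *t* test; 2.367 for Tukey, which is q(0.95; 3, 154)/√2.

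**1. Bias when only one arm is split**

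With no disclosure effect, the expected change is *g* in risk carriers, 0 in non-carriers and *pg* in the unsplit control group.
- Risk subset minus control: *g* − *pg* = *g*(1 − *p*)
- Non-risk subset minus control: −*pg*
- Whole arm minus control: *pg* − *pg* = 0

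At *p* = 0.5 the two planned contrasts are off by +0.15 and −0.15 SD for *g* = 0.3, and by +0.25 and −0.25 SD for *g* = 0.5.

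**2. False differences with no disclosure effect** (simulation, 20,000 trials per setting, *p* = 30%, 50% and 70%)

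| Genotype shift | At least one Tukey contrast with control | Whole-arm test |
|---|---|---|
| 0 | 3.4–3.6% | 4.7–5.0% |
| 0.3 SD | 10.7–11.2% | 4.9% |
| 0.5 SD | 26.8–27.3% | 4.8–5.2% |

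Hand check at *p* = 0.5: the subset SE is √(1/52 + 1/52) = 0.196.
- *g* = 0.5: 0.25/0.196 = 1.27, and P(Z > 2.367 − 1.27) ≈ 0.137 per contrast. The shifts are opposite, so the two nearly add, to about 27%.
- *g* = 0.3: 0.15/0.196 = 0.765, and P(Z > 1.60) ≈ 0.055 per contrast, about 11% together.

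**3. Precision, and what it depends on**
- Whole arm: SE = √(1/105 + 1/52) = 0.170; detectable (1.975 + 0.842) × 0.1696 = 0.48 SD.
- Half-size subset versus control, Tukey: (2.367 + 0.842) × 0.1961 = 0.63 SD.
- Same subset, unadjusted: (1.975 + 0.842) × 0.1961 = 0.55 SD. So (0.63 − 0.55)/(0.63 − 0.48), about half the gap, is due to the Tukey adjustment.
- If only the risk half responds, the whole-arm test needs 0.478/0.5 = 0.96 SD among responders, against 0.63 SD for the Tukey contrast.

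**4. Genotype-matched contrast at *p* = 0.5**
- About 52 intervention versus 26 controls: SE = √(1/52 + 1/26) = 0.240, against 0.196 for the unsplit comparator.
- Detectable, before any multiplicity adjustment: (1.975 + 0.842) × 0.240 = 0.68 SD.

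**The case against.** A reader might infer that the plan contains no test at all of the randomised question. The documents do not support that. The risk and non-risk subsets together make up the intervention arm, and both are tested against the randomised control group on change in intake. The weakness is the comparator.

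Nor is there a flat contradiction with the Summary. Its sentence ends by referring to genotype-tailored advice, so comparing each genotype group with control is a reasonable way to carry it out. The model item is also terse rather than exclusionary: Tukey's test needs a fitted group factor, from which a pooled contrast could be drawn. It is fair to say the contrast is unspecified, but not that it was deliberately rejected.

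Precision is not a one-sided argument either. The intervention reports carry different messages by genotype, so the pooled contrast averages over them. If only risk carriers respond, the plan's own contrast is the more sensitive. At risk shares of 20, 30, 50 and 70%, the pooled test needs about 2.4, 1.6, 0.95 and 0.68 SD among responders (0.475 SD, the normal-approximation figure, divided by the share). The Tukey risk contrast needs 0.83, 0.72, 0.63 and 0.58 SD.

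Finally, the bias exists only if genotype alters change in intake, and the 0.3–0.5 SD shifts are assumed. All of this stands. It narrows the point but does not answer it: the case for looking by genotype is a case for splitting the controls as well.

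**Conclusion.** The concern holds in a limited form. On change in intake, the final plan specifies neither the whole-arm contrast that the Summary describes nor a like-for-like genotype contrast. The contrasts it does specify attribute differences to disclosure correctly only if genotype itself leaves change in intake unaffected.

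If that condition holds, error control is sound, at about 3.5%. If genotype shifts change by 0.3 to 0.5 SD, the chance of at least one false difference from control rises to about 11% to 27% per nutrient and time point, while the whole-arm test stays near 5%. These figures rest on 105 versus 52, no dropout, risk shares of 30–70% and shifts that the documents do not give.

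The main gain from the change is freedom from this bias. A gain in precision (0.48 against 0.63 SD at a 50% share) follows only if both genotype groups respond similarly, and about half of it reflects Tukey's adjustment.

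**What to change.** For each of the four nutrients at 3 and 12 months:

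1. Add intervention versus control in all randomised participants, analysed by assigned arm, as the first between-group test.
2. Then fit an arm-by-genotype model with controls classified by their own genotype. Report risk versus risk, non-risk versus non-risk, and the interaction.
3. State the multiplicity rule that covers both steps, including whether step 2 depends on the result of step 1. Making it depend would be costly if only one genotype group responds.

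Step 1 costs one contrast per model. Step 2 costs more: about 52 controls must be classified for each nutrient, leaving about 26 per cell at a 50% share, and the matched SE rises from 0.196 to 0.240 SD. The Summary says genotypes were determined in the parent study, so no new sampling appears to be needed; the sponsor should confirm that control genotypes are available for this use. The arm average will understate an effect confined to one genotype group, which is why step 2 stays.

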**References:**

1. Sterling R (2008) The online promotion and sale of nutrigenomic services. Genet Med. 10:784-796.

1. **Original trial protocol**

- 200 subjects (aged 20-35 years) will be recruited from the Toronto Nutrigenomics and

Health Study.

- Exclusion criteria:

o <100 mg of caffeine/day

o <10% energy from total sugars/day

o <1500 mg of sodium/day

o Vitamin C supplement use

o Pregnant/nursing

- Subject characteristics (age, sex, ethnicity, level of education) will be collected using a

questionnaire.

- A food frequency questionnaire (FFQ) will be collected at 0, 3 and 12 months.
- Subjects will be randomized to an intervention group or control group (2:1 ratio) and

dietary advice reports will be given.

- Control group: general dietary recommendations for caffeine, vitamin C, added

sugars and sodium.

- Intervention group: DNA-based dietary recommendations for caffeine, vitamin C,

added sugars and sodium.

- Copy of dietary advice reports given at monthly intervals.

**Final protocol:**

Same as original protocol except 157 subjects were recruited.

S**ummary of changes:**

No changes were made to the original study protocol. 157 subjects were recruited instead of the

original goal of 200. Routine updates were made to the protocol’s trial record on

http://clinicaltrials.gov (NCT01353014) to reflect study progress (e.g. enrolment status,

anticipated follow-up and completion dates, actual follow-up and completion dates).

1. **Original statistical analysis plan**

- Subject characteristics between the intervention and control group will be compared using

a Student’s t-test for continuous variables (age) and a Chi-square test for categorical

variables (sex, ethnicity, level of education).

- General linear model will be used to identify changes in the mean intakes of caffeine,

added sugars, vitamin C and sodium from baseline to 3 months and baseline to 12 months.

- Tukey’s test for multiple comparisons will be applied to determine whether changes in

intake of the intervention risk and intervention non-risk groups differ from the change in

intake of the control group.

**Final statistical analysis plan (changes from original plan are indicated in bold):**

- Subject characteristics between the intervention and control group will be compared using

a Student’s t-test for continuous variables (age) and a Chi-square test for categorical

variables (sex, ethnicity, level of education).

- General linear model used to identify changes in the mean intakes of caffeine, added

sugars, vitamin C and sodium from baseline to 3-months and baseline to 12-months.

- Tukey’s test for multiple comparisons applied to determine whether changes in intake of

the intervention risk and intervention non-risk groups differed from the change in intake of

the control group.

- **General linear model used to compare baseline intakes of caffeine, vitamin C, added**

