**sugars and sodium between ethnic groups (Caucasian, East Asian and South Asian).**

- **Ethnicity was adjusted for in dietary intake analyses if a significant difference was**

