**observed at baseline between ethnic groups.**

**Summary of changes:**

- General linear model used to compare baseline intakes of caffeine, vitamin C, added sugars

and sodium between ethnic groups (Caucasian, East Asian and South Asian). Ethnicity was

adjusted for in dietary intake analyses if a significant difference was observed at baseline

between ethnic groups.

- - **Rationale:** A significant difference in baseline nutrient intake was observed

between two ethnic groups. Therefore, we modified our statistical analysis plan to

include ethnicity as a covariate in the general linear model used to identify

changes in nutrient intakes.

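### The final SAP names no own-baseline covariate in its change-from-baseline models, which costs precision and over-corrects chance baseline imbalance between the randomised arms

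*Supplement*

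**What the plan says.** The second bullet of the Final statistical analysis plan sets the outcome and the model: "General linear model used to identify changes in the mean intakes of caffeine, added". The bullet goes on to the other three nutrients and to the two intervals, each starting at baseline and ending at month 3 or month 12. It lists no model terms.

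The third bullet gives the group comparison: "Tukey’s test for multiple comparisons applied to determine whether changes in intake of". Two subgroups of the intervention arm, those with and those without the risk genotype, are each set against the controls.

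The only covariate named anywhere is ethnicity, and it depends on a test: "Ethnicity was adjusted for in dietary intake analyses if a significant difference was". The test in question compares baseline intakes across the ethnic groups. The rationale under Summary of changes says the plan was altered to "include ethnicity as a covariate in the general linear model used to identify". Own baseline intake is not mentioned there.

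Own baseline intake is available. The Original trial protocol, which the Final protocol keeps, states: "A food frequency questionnaire (FFQ) will be collected at 0, 3 and 12 months". The Summary of trial has all participants completing the baseline questionnaire. The Final protocol gives the size: "Same as original protocol except 157 subjects were recruited". The Original trial protocol gives the allocation: "Subjects will be randomized to an intervention group or control group (2:1 ratio) and".

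**The concern.** Questionnaire intake varies within a person from one occasion to the next, so high baseline values tend to be followed by lower ones. A change score subtracts the whole baseline value, although only a fraction r of a baseline deviation is expected to persist to follow-up. This has two consequences for the intervention-versus-control comparison described in the Summary of trial.

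- The residual variance is larger than it need be, in a trial that recruited 157 against a goal of 200.
- If one arm starts higher by chance, regression to the mean makes its change look more negative, and this is read as part of the effect.

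The ethnicity term does not stand in for the missing covariate. It was added because baseline intake differed between ethnic groups, so it adjusts for something related to baseline intake and leaves out the measured value itself. The planned between-arm comparison of characteristics covers age, sex, ethnicity and education, so an imbalance in baseline intake would not be looked for either.

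**Working it through.** The plan has no figure to reproduce: the documents give no alpha, power, effect size, SD, correlation or sample-size derivation.

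**Inputs from the documents.** 157 participants, 2:1, so about 105 intervention and 52 control; intake measured at 0, 3 and 12 months; change as the outcome.

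**Assumptions, not in the documents.** Equal SD s at baseline and follow-up; r from 0.5 to 0.8; no dropout; for the power illustration, a true effect of 0.35 s and two-sided 5%.

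**1. Precision.** The residual variance of a change score is 2s²(1-r). With baseline as a covariate it is s²(1-r²). The ratio is (1-r²)/[2(1-r)] = (1+r)/2. The equivalent change-score sample size is 157 × 2/(1+r).

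| r | Variance ratio | Reduction | Equivalent N |
|---|---|---|---|
| 0.5 | 0.75 | 25% | 209 |
| 0.6 | 0.80 | 20% | 196 |
| 0.7 | 0.85 | 15% | 185 |
| 0.8 | 0.90 | 10% | 174 |

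A simulation of 4,000 trials of 52 versus 105 gave ratios of 0.76 at r = 0.5 and 0.86 at r = 0.7, in line with the formula.

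**2. Power for the randomised arms, 105 versus 52.** The standard error is √(1/105 + 1/52) = 0.170 times the residual SD. Power is Φ(0.35/SE - 1.96).

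- r = 0.5: residual SD 1.000 s without and 0.866 s with the covariate; power 54% and 66%.
- r = 0.7: residual SD 0.775 s and 0.714 s; power 76% and 82%.
- r = 0.8: residual SD 0.632 s and 0.600 s; power 90% and 93%.

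**3. Power on the scale of the SAP's Tukey contrasts.** Assume the intervention arm splits evenly into risk and non-risk (the documents give no split), so about 52 versus 52. The standard error factor is √(2/52.3) = 0.195 and the Tukey critical value for three groups is 2.37. The same 0.35 s effect gives 28% and 38% at r = 0.5, and 48% and 55% at r = 0.7.

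**4. Chance imbalance.** Given a baseline difference D (intervention minus control), the change-score contrast is shifted by -(1-r)D. The SD of a chance D is 0.17 s. A one-SD imbalance therefore shifts the contrast by 0.085 s at r = 0.5, 0.051 s at r = 0.7 and 0.034 s at r = 0.8, opposite in sign to D. In the simulation the slope of the estimate on D was -0.49 (r = 0.5) and -0.30 (r = 0.7) without the covariate, and about 0 with it.

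**5. Where the covariate can mislead.** Risk and non-risk are defined by genotype, and each is compared with all controls. Suppose the true baseline means of two such groups differ by D, the difference is stable, and there is no effect. The change score is then centred on zero, while the adjusted estimate is shifted by (1-r)D. With D = 0.25 s and r = 0.6 that is 0.4 × 0.25 = 0.10 s. A simulation gave 0.00 for the change score and 0.10 s for the adjusted estimate.

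**The case against.** Change from baseline is a legitimate estimator in a randomised trial. Over repeated randomisations the intervention-versus-control contrast is unbiased and its type I error is correct. This stands, and it limits the point to precision and to bias conditional on the imbalance that occurred.

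The plan's bullet is one sentence long and does not rule out a baseline term. This also stands: the adjustment is unspecified. But the model was reopened to add a covariate because of baseline intake differences, and own baseline intake was still not named, so brevity is not a full answer.

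Three stronger readings are tempting, and the documents support none of them.

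- A reader might infer that chance imbalance goes uncorrected. Subtracting baseline does act on it; when r is below 1 it goes too far.
- A reader might take the 105-versus-52 powers as the power of the planned analysis. The SAP's contrasts split the intervention arm and use Tukey's test, where the powers are much lower, though the gain remains.
- A reader might infer that adjusted estimates should replace change scores throughout. Nothing in the documents says that controls are divided by genotype, so risk or non-risk against all controls is not purely randomised. The Summary of trial describes variants that influence sugar consumption, so stable baseline differences are plausible, and there adjustment has its own bias (step 5).

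The size also depends on r. At r = 0.8 the variance gain is only 10%.

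**Conclusion.** The point holds as a should-fix. The final SAP leaves own baseline intake out of the covariates it names, although the data are collected on everyone. For the randomised intervention-versus-control comparison, adding it would cut the variance by about 25% to 10% for r between 0.5 and 0.8, and would remove a conditional shift of -(1-r)D. These sizes rest on equal SDs at baseline and follow-up, no dropout and an assumed range for r; the powers also rest on an assumed effect of 0.35 s. The planned test is not invalid, and the case for adjustment does not carry over without qualification to the risk and non-risk contrasts against all controls.

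**What to change.** 1. For each nutrient, name the participant's own baseline intake as a covariate in the 3-month and 12-month models, whatever any baseline significance test shows.
2. Report baseline-adjusted intervention-versus-control differences with 95% CIs.
3. For the risk and non-risk contrasts, compare with controls of the same genotype where their genotypes are available; the Summary of trial says that genotypes were determined from the blood samples given in the parent study. Otherwise, show the change-score result beside the adjusted one and say that the two can differ if true baseline means differ.
4. If outcome data have already been analysed, label the adjusted model as a later change and keep the change-score result in the report.

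The cost is one model term and one degree of freedom per model, with no new data collection. Item 3 adds a second set of estimates, or smaller comparison groups if controls are matched on genotype.

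### Tukey's all-pairs test is valid but conservative for the two comparisons with control that the SAP names; Dunnett's test would be modestly more efficient

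*Supplement*

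**What the plan says.** The final statistical analysis plan models change in four nutrients over two intervals. That item opens "General linear model used to identify changes in the mean intakes of caffeine, added"; it goes on to name the remaining nutrients and sets the two intervals as baseline to month 3 and to month 12. For multiplicity, the next item calls on Tukey's procedure, in the words "test for multiple comparisons applied to determine whether changes in intake of". It then identifies the comparison: "the intervention risk and intervention non-risk groups differed from the change in intake of", with controls as the reference.

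The original plan names the same test for the same purpose. The one addition in the final plan is an ethnicity adjustment, made where baseline intakes differ between ethnic groups.

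On the design, the protocol states "Subjects will be randomized to an intervention group or control group (2:1 ratio) and" the final protocol records "Same as original protocol except 157 subjects were recruited", against a goal of 200.

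The documents do not state a significance level, a power calculation, the expected split of the intervention arm by genotype, or a reason for an all-pairs procedure.

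**The concern.** Three groups give three pairs: risk against control, non-risk against control, and risk against non-risk. The plan poses only the first two as questions, and the trial summary likewise sets intervention against control. Tukey's critical value protects all three pairs. Dunnett's test is built for several groups against one control, and it holds the same nominal familywise error over just those contrasts with a smaller critical value.

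What is at stake is efficiency. Every control contrast is judged against a stricter cut-off than the stated questions need, and this recurs for each nutrient and each interval. About a third of the participants are controls, and each contrast uses only part of the intervention arm, so a cheap gain in precision is worth having.

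**Working it through.** The plan has no figure of its own to reproduce, so the two procedures are compared directly.

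**Inputs from the documents**
- Participants: 157 (final protocol).
- Allocation 2:1 (original protocol, retained in the final one): 157/3 ≈ 52 control, leaving 105 intervention.
- Families: 4 nutrients × 2 intervals = 8 (final SAP).

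**Assumptions, because the documents are silent**
- 5% two-sided familywise error within each nutrient-by-time family.
- All 157 analysed, so residual df = 157 − 3 = 154, ignoring the few df that an ethnicity term would use. A case with 120 analysed is shown as well.
- Risk:non-risk split from 20:80 to 80:20, as it will differ by gene.

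**Step 1. Tukey.** Critical |t| = q(0.95; 3 groups, 154 df)/√2 = 3.347/1.414 = 2.367.

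**Step 2. Dunnett.** Critical |t| is the c that solves P(max(|T₁|, |T₂|) > c) = 0.05. The two statistics are correlated through the shared control by ρ = √[n₁/(n₁+n₀) × n₂/(n₂+n₀)].
- Split 52/53: ρ = √(52/104 × 53/105) = 0.502, c = 2.232.
- Split 21/84 (or the reverse): ρ = √(21/73 × 84/136) = 0.422, c = 2.241.

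**Step 3. Error that Tukey actually spends on the two wanted contrasts.** Putting c = 2.367 into the Step 2 probability gives 0.0358 (even split) and 0.0365 (20:80). Simulation with 200,000 runs gave 0.036 over the two contrasts, and 0.048 to 0.050 over all three pairs. About 1.4 points of a 5% allowance go unused.

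**Step 4. Interval width.** 1 − 2.232/2.367 = 5.7%; 1 − 2.241/2.367 = 5.3%.

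**Step 5. Power.** With the noncentral t on 154 df, Tukey has 80% power at noncentrality 3.21. At that same value Dunnett has 83.5% (even split) or 83.3% (20:80).

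**Step 6. Sample size for 80% power.** Ratio = ((c_Dunnett + 0.842)/(c_Tukey + 0.842))².
- Even split: (3.074/3.209)² = 0.918.
- 20:80: (3.083/3.209)² = 0.923.

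So Dunnett needs about 8% fewer participants for equal power.

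**Step 7. Sensitivity.** Power per contrast by standardised difference, 52/52/53:

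| Difference | Dunnett | Tukey |
|---|---|---|
| 0.3 | 24.4% | 20.5% |
| 0.4 | 42.6% | 37.4% |
| 0.5 | 62.5% | 57.3% |
| 0.6 | 79.5% | 75.5% |
| 0.7 | 90.8% | 88.4% |
| 0.8 | 96.7% | 95.6% |

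The gap is 1 to 5 points. With 120 analysed (40 per group), critical values are 2.374 and 2.239, and power at a difference of 0.5 is 50.1% against 44.8%. Dunnett's critical value was the smaller in every case tried.

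**The case against.** The strongest reply is that nothing is wrong: Tukey protects both stated contrasts, was specified from the outset, and errs on the safe side. That stands as far as validity goes. A reader might infer from the mismatch that the analysis is unsound or that false positives are inflated. The calculation shows the opposite, since error over the two contrasts is about 3.6% where 5% is allowed.

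A second reply is that Dunnett's gain is not free. Its nominal error rate is the same, but on the wanted contrasts the actual rate rises from about 3.6% to 5%, and the plan states no adjustment across the eight families. If those were independent, the chance of at least one false positive over the control contrasts would go from 1 − 0.964⁸ = 25% to 1 − 0.95⁸ = 34%. The outcomes are probably correlated, so these figures are only illustrative, and the gap across families exists under either test. The cost is real, but it is acceptable if 5% per family was the intention.

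A third reply concerns timing. The final plan is worded in the past tense and reports a baseline difference already seen. Moving to a more powerful test at that stage needs a stated reason and a record. This stands too, and keeping the specified test would be defensible.

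A reader might also take recruitment of 157 rather than 200 as proof that the trial lacks power. The documents give no effect size, SD or power target, so they cannot show that.

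Nor would dividing the controls by genotype be an easy alternative. It answers a different question from the one in the SAP, and halving the control group in a comparison of about 52 with 52 raises the standard error by √1.5, about 22%. That far outweighs a 5 to 6% gain in critical value.

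**Conclusion.** The point holds as a modest loss of efficiency, with no fault of validity. The direction rests on the SAP's own wording: two contrasts with one control, and no request for the third pair. The size is illustrative, because alpha, the genotype split and retention are assumed, but it changed little over splits from 20:80 to 80:20 or with 120 analysed. If the investigators do want inference on risk against non-risk, Tukey is a reasonable choice and the only defect is that the SAP does not name that contrast.

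**What to change.** Choose one of two wordings in the final SAP.

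1. If only the comparisons with control matter, specify Dunnett's two-sided test against control on the general linear model means, ethnicity-adjusted where the plan calls for that adjustment.
2. If risk against non-risk is also wanted, add it as a stated contrast and keep Tukey.

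In either case, state the familywise alpha and that it applies within each nutrient-by-time family. Error across the eight families is a separate decision that neither test settles.

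Before data are seen, the first option costs a short text edit and a software option, and no stated comparison is lost. If outcome data have already been seen, record the date and reason for the switch and report the Tukey result beside the Dunnett result.
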